## Objectives

This study will consist of a longitudinal observational study that will assess the evolution of the PNSC (i.e., CRF, emotional distress, pain, sleep difficulties) in two cohorts of patients who had cancer (women with breast cancer and patients with digestive cancer), over two years, through network analyses. Evolution of other common symptoms (e.g., cognitive difficulties, nausea/vomiting, appetite loss), QOL, coping strategies, and self-compassion will be assessed in parallel. To note, the results from this study, especially the core symptom determined in each cohort, will be used in a future study to develop a new mind-body group intervention based on the common-sense model of self-regulation of health developed by Leventhal [31]. A randomized-controlled pilot trial will then be conducted to assess its feasibility and first benefits to improve the PNSC.

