### Eligibility

Inclusion criteria will be: ≥18-years-old, fluent in French, diagnosis of non-metastatic breast cancer or digestive cancer (i.e., anal, colorectal, gastric, oesophageal, liver, pancreatic cancers), no history of cancer and not currently in relapse, time since end of active treatments (i.e., surgery, chemotherapy, radiation therapy) < 5 years (based on the methodology and recommendations of previous studies on symptom clusters in oncology [2, 3, 35, 37]). Breast and digestive cancer were chosen because they are among the most common cancers [38]. Thus, they would be easier to recruit, and our results could be of interest for more patients, as well as their relatives and healthcare professionals. Metastatic cancers will not be included, as done in one of our previous studies [26], in order to minimize the baseline differences in the sample, as the changing nature and complexity of metastatic cancers could make it difficult to compare the results with non-metastatic cases [39].

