### Assessments

Approximate duration of questionnaires completion is 20 min at each measurement time. First, socio-demographic and medical data will be collected (i.e., sex, age, marital situation, education level, professional activity, cancer diagnosis, cancer stage, personal history of cancer and treatments, possible recurrence during the study, comorbidities, neurological and psychiatric history, history of drug or alcohol abuse, previous participation in a mind-body intervention, psychotherapy, major life events). Symptoms involved in the PNSC, as well as other common symptoms and QOL, will be assessed as follows:

*European Organization for Research and Treatment of Cancer - Quality of Life Core Questionnaire-30 (EORTC QLQ-C30)* [40]: This questionnaire (30 items) assesses the QOL of patients with cancer through 5 functional scales (physical, role, emotional, cognitive, and social functioning), three symptom scales (fatigue, nausea and vomiting, pain), a global health status/QOL scale and several single items for additional difficulties (dyspnoea, insomnia, appetite loss, constipation, diarrhoea, financial difficulties). Each item is scored on a 4-point Likert scale (‘not at all’ to ‘very much’), excepted for the global health status/QOL that is a 7-point scale (‘very bad’ to ‘excellent’). For functional scales and QOL scale, higher scores indicate better functionality and QOL. For symptom scales and single items, higher scores indicate higher symptomatology.*Multidimensional Fatigue Inventory (MFI-20)* [41]: This 20-item scale is designed to measure fatigue on 5 dimensions: general fatigue, physical fatigue, mental fatigue, reduced motivation and reduced activity. Suggested cut-off scores for significant general fatigue have been proposed for the general population: ≥ 11 (for men between 40 and 59 years-old), ≥ 12 (for women between 40 and 59 years-old), and ≥ 14 (for men and women older than 60 years-old) [42, 43].*Hospital Anxiety and Depression Scale (HADS)* [44]: This 14-item scale measures anxiety and depression, and has been validated for people with somatic illnesses. Scores between 8 and 10 on a dimension suggest the presence of anxious and/or depressive disorders, while scores between, 11 and 21 indicate the presence of such disorders.

Other variables of interest (i.e., coping strategies and self-compassion) will be assessed as follows:

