### Statistical analyses

Normality of data will be checked using Shapiro-Wilk test. Sociodemographic and medical data will be described using frequencies and percentages, means and standard deviations, or medians and interquartile ranges, depending on the distribution. To estimate the networks’ structure, a standardized score (z score [1]) will be calculated for each variable or dimension. Three centrality indices will be used: strength (number and strength of the direct connections to a node/symptom, i.e., sum of absolute weights; a high strength means that the symptom is more likely to occur in conjunction with other symptoms), closeness (node’s relationship to all other nodes; closer nodes mean stronger correlation), and betweenness (importance of a node in the average pathway between other pairs of nodes; a node with a higher betweenness has greater influence in the network) [1, 2]. Symptom networks will be created for both cohorts, at each of the four measurement times. To assess the differences between two networks (i.e., between breast and digestive cancers), and over time for each cohort (i.e., between T1, T2, T3 and T4), network comparison tests will be used [1, 17]. The evolution of the other variables over time (i.e., self-compassion, self-care agency, self-care strategies already implemented to manage CRF, and the representations about CRF) will also be measured and compared through repeated measures MANOVA and post-hoc comparisons.

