The present study will suffer from several limitations. First, as no standard procedure to determine the ideal sample size for network analyses exist, we based our calculation on existing studies with similar methodology. It is then possible that the sample size will remain too small to allow robust results. Second, we decided to include patients who completed their active treatment within the last 5 years. One could argue that 5 years is a rather long period of time, that the psychological state and quality of life of patients are very likely to evolve during that time, and that the participants would be very different from each other, leading to an unexpected heterogeneity of our sample. However, the threshold of 5 years is commonly used in oncology studies, as it is considered to distinguish the “short-term” and “long-term” cancer survivors [2, 35, 48]. Our decision is thus in line with existing practices in the field. Finally, we will focus on two populations of cancer patients only (i.e., survivors of breast or digestive cancer). These results will then be relevant to these patients only. However, breast and digestive cancers are among the most frequent cancers [38], making our results applicable for many patients and health professionals.

Despite these limitations, this study will be one of the first to assess over a long period of time the evolution of the PNSC on two distinct populations. As described, the conduction of the present study will allow us to design a new multi-component intervention specifically targeting the core symptom determined in each cohort, and to assess its feasibility and preliminary benefits. Taken as a whole, this project is thus particularly original, timely relevant and innovative. It will bring new knowledge about the PNSC, its evolution, and its specificities according to the diagnosis, and its results will open a lot of scientific and clinical perspectives to improve symptom (self-)management of patients with cancer.

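### As described, the breast versus digestive network comparison cannot separate diagnosis from sex, and differences between waves may partly reflect recurrence; no check on either is stated

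*Protocol article*

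**What the plan says.** **Cohorts.** The Objectives describe the two cohorts as "women with breast cancer and patients with digestive cancer". The Eligibility section asks only for a "diagnosis of non-metastatic breast cancer or digestive cancer" and sets no sex limit for either cohort.

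**Entry conditions.** Both cohorts share the same window, "time since end of active treatments (i.e., surgery, chemotherapy, radiation therapy) < 5 years", and the same condition, "no history of cancer and not currently in relapse".

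**Data collected.** The Assessments section lists sex, age, stage, treatment history and "possible recurrence during the study". The only use of sociodemographic and medical data given under Statistical analyses is descriptive.

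**Analysis.** "Symptom networks will be created for both cohorts, at each of the four measurement times", which makes eight networks. Network comparison tests are then applied between the cohorts ("To assess the differences between two networks (i.e., between breast and digestive cancers") and between waves within each cohort. The article names no restriction, adjustment or sensitivity analysis for either contrast.

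**Interpretation.** The Discussion expects networks to differ by cohort and by measurement time, and says the study will inform about the cluster and "its specificities according to the diagnosis".

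**The concern.** Each contrast changes more than the factor it is meant to study.

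- **Between cohorts.** Under the Objectives, moving from breast to digestive changes the diagnosis and also moves from women only to a mixed group. If men and women differ in symptom level, or in how symptoms relate to each other, the networks can differ for that reason alone.
- **Between waves.** T1 is free of relapse by design, and T2 to T4 need not be. If participants with a recurrence have worse symptoms on several scales at once, correlations at later waves rise. That runs against the weakening over time which the Discussion offers as an example of what it expects.

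What is at stake is interpretation. The study is meant to describe diagnosis-specific networks and their evolution, and a later intervention is to be built on the most central symptom in each cohort.

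**Working it through.** **Step 1: the text.** Objectives: breast cohort women, digestive cohort unrestricted. Statistical analyses: whole cohorts compared. Discussion: result read by diagnosis. With sex constant in one cohort and mixed in the other, the all-participant contrast contains diagnosis and sex together. If Eligibility governs instead, men with breast cancer may enter, and the sex mix is still not made equal.

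**Step 2: a rough size.** The plan has no figure on this point to reproduce. The only input from it is the target of 200 per cohort (Design and procedures). The sex split, recurrence proportion and symptom shifts below are assumptions.

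Suppose a fraction *p* of a group is shifted by *d* standard deviations on both of two symptoms whose within-subgroup correlation is *r*. The observed correlation is then

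r′ = (r + k)/(1 + k), with k = p(1 − p)d².

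Worked cases at r = 0.35:

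| Source | p | d | k | r′ | Rise |
|---|---|---|---|---|---|
| Sex (digestive cohort) | 0.50 | 0.3 | 0.0225 | 0.364 | 0.014 |
| Sex (digestive cohort) | 0.50 | 0.5 | 0.0625 | 0.388 | 0.038 |
| Recurrence by T4 | 0.10 | 0.8 | 0.0576 | 0.385 | 0.035 |
| Recurrence by T4 | 0.20 | 0.8 | 0.1024 | 0.410 | 0.060 |

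Wider ranges with the same formula:

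- Sex, 40–60% men and d = 0.2–0.6: a rise of 0.007–0.058 at r = 0.30, and 0.010–0.083 at r = 0.
- Recurrence, 5–15% and d = 0.5–1.0: a rise of 0.008–0.079 at r = 0.30, and 0.012–0.113 at r = 0.

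**Step 3: against sampling error.** For one correlation in two independent groups of 200, SE of the difference = √(2/200) × (1 − 0.35²) = 0.1 × 0.8775 = 0.088. The difference detectable with 80% power at two-sided 5%, on the Fisher z scale, is (1.96 + 0.84) × √(1/197 + 1/197) = 0.28. Each shift is below what one edge could show. Both figures assume independent groups, so they apply to the cohort contrast; the wave contrasts use the same people, and there they are only a guide.

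**Step 4: partial correlations.** The article does not say which kind of edge is estimated. With 10 nodes all correlated at r, each partial correlation is r/(1 + 8r):

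- r = 0.35: 0.35/3.80 = 0.092
- r = 0.388: 0.388/4.104 = 0.095
- r = 0.41: 0.41/4.28 = 0.096

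A shift common to all symptoms therefore largely cancels in such a network.

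**Step 5: what this leaves out.** The formula covers only shifts in mean level. It says nothing about sex or recurrence changing the associations themselves, for which the documents give no information.

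**The case against.** **The article is condensed.** Covariate sets and sensitivity analyses are commonly left to a fuller plan. This stands: the lack of a covariate list is no finding, and the article does not say that adjustment is ruled out. But it does define cohorts of different sex composition, describe a whole-cohort comparison and announce a reading by diagnosis. Those three statements do not fit together without a further step.

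**The cohorts as they are may be the right target.** For designing an intervention for each population, its actual network, with its natural sex mix and later recurrences, is legitimate. This also stands. It is why the all-participant analyses should remain primary, and why the problem is confined to attributing differences to diagnosis or time.

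**The shifts are small.** True per edge under the assumed values, and more so for partial correlations. It limits the weight of the point but does not make the two explanations separable.

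**Stronger readings that the documents do not support.**

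- A reader might infer that time since treatment is also confounded with cohort. Both cohorts share the same window of under 5 years, and nothing shows that they differ within it.
- A reader might see a defect in participants passing 5 years during follow-up. The limit is an entry criterion, and the Discussion already acknowledges the heterogeneity that the window brings.
- A reader might think relapsed patients join after T1. Nobody does; participants enrolled free of relapse may relapse and stay in the study.
- A reader might see later recurrence as contradicting the exclusion of metastatic disease. The stated reason for that exclusion concerns baseline differences.

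**Conclusion.** The point holds in a limited form. As written, a breast versus digestive difference cannot be credited to diagnosis apart from sex. This follows from the cohort definitions in the Objectives and needs no assumed number. A T1–T4 difference may partly reflect recurrence, which is absent at T1 by design and possible afterwards; how much depends on how many participants relapse.

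The size of either effect is unknown. Under the assumptions shown, it is about 0.01–0.06 (sex) or 0.01–0.08 (recurrence) on a correlation of 0.30, and up to about 0.08 and 0.11 where the underlying correlation is zero. It is a few thousandths for partial correlations in the 10-node example. A reader might infer that whole networks will be visibly distorted. The figures do not show that, and they would need every symptom to shift in the same direction. The mismatch on sex between Objectives and Eligibility is a plain inconsistency in the text.

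**What to change.** 1. **Add a women-only breast versus digestive network comparison** as a sensitivity analysis, and make diagnosis-specific statements only if it agrees with the all-participant result. Adjusting for sex within each cohort would not do the same job: where sex is constant, it can be neither a node nor a useful covariate. The cost is precision. If 40–60% of 200 digestive completers are women (80–120), the detectable Fisher z difference for one correlation rises from 0.28 to 0.38 (200 versus 80) or 0.33 (200 versus 120). Agreement should therefore be judged on the estimates, not on whether significance is retained.

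2. **Keep all participants in the primary wave comparisons**, and repeat the T2–T4 networks and contrasts without participants who have had a recurrence, as a sensitivity analysis. This should not become the primary analysis: it conditions on an event after baseline and leaves a selected relapse-free group. If 10–20% of 200 had relapsed by T4, 160–180 would remain.

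3. **Reconcile the sex criterion for the breast cohort** between Objectives (women) and Eligibility (no sex limit). Eligibility is checked within the online questionnaire, so its wording decides who enters.

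Items 1 and 2 use sex and recurrence data that the study already collects. They cost analysis time and a few sentences in the plan.

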*Ways of Coping Checklist* [45, 46]: This 27-item scale assesses coping through 3 dimensions: problem-oriented coping (score range: 10–40), emotion-oriented coping (score range: 9–36), and seeking social support (score range: 8–32). Higher scores indicate higher use of specific coping strategies.*Self-compassion scale* [47]: This 26-item questionnaire measures 6 dimensions related to self-compassion: self-kindness, self-judgment, common humanity, isolation, mindfulness, and over-identification, with higher scores indicating higher self-compassion. A total mean score is also generated and indicates low (i.e., score between 1 and 2.49), moderate (i.e., score between 2.5 and 3.49), or high (i.e., score between 3.5 and 5) self-compassion.

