## Discussion

Recent studies highlighted the prevalence and negative consequences of the PNSC in oncology [1–3]. The core symptom of this cluster could be of major importance in the management of the cluster of symptoms as a whole [22] but it is still unclear which symptom from the cluster is the most central among patients with breast or digestive cancer. Determining this core symptom could allow to develop more cost-effective interventions, as addressing this symptom will likely decrease the other symptoms from the cluster [1–3, 11, 17, 18, 20, 23]. The development of multi-component interventions, especially those aiming to manage the whole PNSC, is then urgently needed in oncology [11]. We thus designed a longitudinal study assessing the PNSC and other symptoms in breast cancer and digestive cancer survivors, over 2 years. We hypothesize that: (1) one dimension of CRF or of emotional distress (i.e., depression or anxiety) will be the core symptom in all the obtained networks (i.e., for both cohorts and at each of the four measurement times), (2) the physical and mental dimensions of CRF will have different relationships with the other symptoms of the networks (e.g., physical fatigue could have stronger relationships with other physical symptoms such as loss of appetite or nausea/vomiting), (3) the configuration of the networks will differ according to the cohort considered (e.g., nausea/vomiting and diarrhoea/constipation could have stronger relationships with CRF, anxiety or depression in the digestive cancer cohort), and the measurement time (e.g., some correlations could weaken over time, as the intensity of some symptoms will decrease and became less important in the networks), and (4) self-compassion and coping strategies will not significantly evolve over time, even if a trend in this sense is possible due to a better adaptation to cancer.

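### The repeated-measures MANOVA lists three outcomes with no described instrument and omits coping, which is half of hypothesis 4

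*Protocol article*

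**What the plan says.** Four places in the protocol article bear on this point.

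- **Statistical analyses.** After the network methods, the section turns to the remaining variables and defines them, after an i.e., as "self-compassion, self-care agency, self-care strategies already implemented to manage CRF, and the representations about CRF". These "will also be measured and compared through repeated measures MANOVA and post-hoc comparisons".
- **Assessments.** The corresponding sentence reads "Other variables of interest (i.e., coping strategies and self-compassion) will be assessed as follows". Two instruments follow. For the Ways of Coping Checklist: "This 27-item scale assesses coping through 3 dimensions". For the Self-compassion scale: "This 26-item questionnaire measures 6 dimensions related to self-compassion", to which the text adds a total mean score. The remaining instruments are the QLQ-C30, the MFI-20 and the HADS.
- **Objectives.** Besides the symptom cluster and other common symptoms, the evolution of "QOL, coping strategies, and self-compassion will be assessed in parallel".
- **Discussion, hypothesis 4.** The prediction is that "self-compassion and coping strategies will not significantly evolve over time".

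**The concern.** The analysis paragraph and the rest of the article describe different sets of variables. Both the analysis list and the Assessments list are introduced by i.e., so each reads as complete, yet they share only self-compassion.

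An analyst who follows the text would look for three outcomes with no described source. The same analyst would have no instruction to analyse coping, which is collected and is the subject of a stated hypothesis. A later report on coping would then depart from the published analysis paragraph, and a report without coping would leave half of hypothesis 4 unanswered. The paragraph also does not say which of the coping and self-compassion scores would carry the test.

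**Working it through.** The article gives no figure to reproduce here, so the check compares lists.

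**1. Listed outcomes against described instruments**

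| Outcome in the MANOVA list | Instrument in Assessments |
|---|---|
| Self-compassion | Self-compassion scale |
| Self-care agency | none described |
| Self-care strategies for CRF | none described |
| Representations about CRF | none described |

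Result: 4 − 1 = 3 of the 4 listed outcomes have no described instrument.

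Two possible hidden sources were checked.
- The socio-demographic and medical items include earlier mind-body participation and psychotherapy, but none is presented as a measure of self-care agency, self-care strategies or representations.
- The Ways of Coping Checklist is scored for problem-oriented coping, emotion-oriented coping and support seeking. It is not described as specific to fatigue or to self-care.

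The Design and procedures section refers the reader to Statistical analyses for more on the questionnaires, but that section names no instrument.

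**2. Hypothesis 4 against the MANOVA list**

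- Constructs in hypothesis 4: self-compassion, coping (2).
- In the MANOVA list: self-compassion (1).
- Result: 2 − 1 = 1 of 2 has no assigned analysis.

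The omitted construct has three scores with ranges 10–40, 9–36 and 8–32. The minima imply 10 + 9 + 8 = 27 items, which agrees with the stated length. The instrument is therefore fully described, and only the link to an analysis is missing.

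**3. The other places that name these variables**

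The abstract, the Objectives, the Assessments and hypothesis 4 all name self-compassion and coping. None of them names the three extra constructs as study variables. Representations do appear in the Background, but as a target for interventions.

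**4. Secondary check: QOL**

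The Objectives also promise the evolution of QOL, which the QLQ-C30 measures: "This questionnaire (30 items) assesses the QOL of patients with cancer through 5 functional scales", together with a global scale. QOL is not in the MANOVA list. The other inferential method is the network comparison test, on networks of standardised variables. For b > 0, corr(a + bX, Y) = corr(X, Y), so a shift in the mean of X leaves its associations unchanged. Even if global QOL were a node, which the text does not say, network comparison would not show whether its level rose or fell.

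**The case against.** The strongest reply is that the intended method for coping can be recognised. The Assessments define the other variables of interest as coping and self-compassion, and Statistical analyses applies the MANOVA to the other variables. Read together, the list in brackets is the error and coping was meant to be included. This is probably right, and it means that hypothesis 4 is not left without a recognisable method. It does not remove the fault: the paragraph commits to a specific list that conflicts with the rest of the article, and a correct analysis plan held elsewhere would not make this text correct.

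The second reply is that the main aim is untouched. That stands. Networks, centrality and network comparison, with hypotheses 1 to 3, do not depend on this list.

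Two stronger readings are tempting, and neither is supported.
- A reader might infer that the three constructs are never measured. The article shows only that no instrument is described for them.
- A reader might infer that changes in the level of every symptom score were promised and left untested. The Objectives assess the cluster through network analyses and say of the other symptoms and QOL only that they are assessed in parallel. No hypothesis concerns mean change in symptoms or QOL. Falling symptom intensity appears in hypothesis 3 only as a reason why correlations might weaken.

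**Conclusion.** The point holds as a contradiction within the article. Three of the four outcomes listed for the repeated-measures MANOVA have no described instrument, and coping, one of the two constructs in hypothesis 4, is missing from the list. This is not detail left to a fuller document: the text fixes a list, and the list disagrees with the abstract, the Objectives, the Assessments and hypothesis 4.

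The effect is confined to one secondary hypothesis and the coping objective. The conclusion assumes that the Assessments section is complete, as its wording implies. If the three constructs are in fact collected, the Assessments are the section at fault on that part, and the omission of coping from the analysis list remains.

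QOL is a side remark only. Its evolution is promised and network comparison does not show change in its level, but a description over time would satisfy the wording of the Objectives.

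**What to change.** 1. In Statistical analyses, replace the list so that it matches the Objectives, the Assessments and hypothesis 4. Name the three Ways of Coping scores and the self-compassion score as the outcomes that test hypothesis 4, and state whether the latter is the total mean score or the six dimensions.
2. Delete self-care agency, self-care strategies and representations about CRF. If they are collected, add their instruments and measurement times to the Assessments instead.
3. Optionally, add the global QOL score to the same longitudinal analysis or state that it will be described over T1 to T4. Tests of every symptom score are not needed; they would add many comparisons that no hypothesis calls for.

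The cost is a change of wording. Coping, self-compassion and QOL already come from the questionnaires described for the four measurement times, so deleting the three constructs needs no new data and no change to the 240 participants per cohort. The correction should be made before the longitudinal data are analysed, so that the choice of scores does not follow the results.

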## Methods

### Design and procedures

We designed a longitudinal observational study to assess the evolution of the PNSC and the respective relevant variables in two distinct cohorts of cancer survivors (breast cancer survivors and digestive cancer survivors). Questionnaires (in French; see “Statistical analyses”for more details) will be completed online (on www.alchemer.eu) at four different times: at inclusion (T1), then 6 (T2), 12 (T3) and 24 (T4) months later. Written informed consent will be obtained from each participant at the beginning of the study (included at the beginning of the online questionnaires), and the inclusion criteria are checked at the beginning of the questionnaires, so that only participants who meet the criteria will be eligible to complete them. Participants will also have the possibility to contact the principal investigators by email or phone if needed (e.g., question, adverse event, or difficulty related to the study). At each measurement time, the risk of missing responses is very low, as the online questionnaires are designed in a way that does not allow for missing answers. The short duration of the questionnaires (approximately 20 min) will also increase completion and retention. All data will be anonymized: a code will be attributed to each participant and used during the entire study. Only the principal investigators involved in this study will have access to the complete datasets. Review of the trial process and difficulties encountered are discussed regularly between the researchers involved. As no standard procedure to determine the ideal sample size for network analysis is commonly used, the number of participants required in this study will be based on other studies in oncology using similar methodology [1–3, 17, 18, 20] and including between 172 and 342 patients per cohort, and set to 200. Accounting for a drop-out rate of 10% at one year in an observational study [36], and likely a higher drop-out rate at two years, we aim to include 240 participants in each cohort.

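### Repeated measures MANOVA for the non-network variables discards everyone who misses a wave, although the plan expects drop-out; a mixed model on all available waves would keep their data

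*Protocol article*

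**What the plan says.** Protocol article, Design and procedures: questionnaires are completed "at inclusion (T1), then 6 (T2), 12 (T3) and 24 (T4) months later". The target per cohort follows earlier network studies "including between 172 and 342 patients per cohort, and set to 200". It is then raised: "Accounting for a drop-out rate of 10% at one year in an observational study", and "likely a higher drop-out rate at two years", so that "we aim to include 240 participants in each cohort". No figure is given for two-year drop-out. On missing data the section says, with reference to each measurement time, that "the risk of missing responses is very low, as the online questionnaires are designed in a way that does not allow for missing answers". It adds that a short questionnaire should help completion and retention.

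Protocol article, Statistical analyses: symptom networks are built per cohort and per wave. The evolution of the other variables is to be measured and "compared through repeated measures MANOVA and post-hoc comparisons". The list in that sentence includes self-compassion. Coping is not in the list, but the fourth hypothesis in the Discussion treats it together with self-compassion and expects no significant change in either. I take it that coping is to be analysed in the same way.

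**The concern.** The named method needs a complete set of waves from each participant, and the design does not promise one. A participant who answers at T1, T2 and T3 and is lost before T4 is removed from the whole MANOVA, including from what it says about T1 to T2 and T1 to T3. Forced answers do not help, because they act only on a questionnaire that has been opened.

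Two things are at stake. Data already collected are thrown away, which widens intervals and weakens tests. For the fourth hypothesis this matters in a particular direction: the expected result is non-significance, so a less precise analysis makes it easier to appear to confirm it. Second, the results describe completers. Recurrence during the study is recorded (Assessments) and is a plausible reason to leave, so it is doubtful that drop-out is unrelated to how people are doing.

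**Working it through.** **Inputs from the document.** Target 200 per cohort; enrolment 240 per cohort; drop-out 10% at one year, higher but unquantified at two years; four waves at 0, 6, 12 and 24 months.

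**Reproducing 240.** Enrolment = target / (1 − loss).
- Loss 10%: 200 / 0.90 = 222.2, so 223. The one-year figure alone does not give 240.
- Solving for the loss: 1 − 200/240 = 16.7%. After 10% in year one (240 × 0.90 = 216), this leaves room for 1 − 200/216 = 7.4% of those remaining in year two.

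So 240 is consistent with a two-year loss of 16.7%, which is higher than 10%, as the text says.

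**Participants removed by a complete-wave analysis**, if losses are pure drop-out:
- 16.7% (implied by 240 and 200): 240 − 200 = 40 per cohort.
- 10% in each year (an assumption): 240 × 0.81 = 194.4 remain, so about 46 removed.
- Other two-year losses (assumptions): 15% leaves 204, 20% leaves 192, 25% leaves 180, 30% leaves 168.

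**Intermittently missed waves** lower this further. If completers also miss T2 and T3 independently at an assumed 5% or 10% each, the 194.4 becomes 194.4 × 0.95² = 175 or 194.4 × 0.90² = 157.

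**Observed pairs discarded.** Under 10% a year, T2 has 240 × 0.90^0.5 = 227.7 and T3 has 216.
- T1–T2: 1 − 194.4/227.7 = 14.6% of pairs lost; standard error larger by √(227.7/194.4) = 1.08.
- T1–T3: 1 − 194.4/216 = 10.0% lost; √(216/194.4) = 1.05.

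With 200 at T4 and the same T2 and T3 sizes:
- T1–T2: 1 − 200/227.7 = 12.2% lost; √(227.7/200) = 1.07.
- T1–T3: 1 − 200/216 = 7.4% lost; √(216/200) = 1.04.

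The ratios are for simple paired differences.

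**Bias, by simulation under assumed inputs.** 240 participants, four waves, correlation 0.7 between waves, log-odds of drop-out rising by 0.7 per SD worse previous score (about a doubling of the odds).

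| Quantity | Complete cases (error, SD) | Maximum likelihood (error, SD) |
|---|---|---|
| Mean at T1 | 0.106 | 0.003 |
| Mean at T4 | 0.099 | 0.005 |
| Change T1–T4 | −0.007 | 0.002 |

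With log-odds from 0.35 to 1.1 the complete-case error at T1 ran from 0.06 to 0.15 SD. The error in the T1–T4 change stayed within 0.02 SD in the scenarios tried. Levels are distorted; change is hardly touched.

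**The case against.** The strongest reply is that this is a modest loss of precision on secondary variables. Fatigue, distress, pain and sleep, the study's main object, are analysed by networks built at each wave, which do not need complete follow-up. The fourth hypothesis is about change, and the simulated bias in change is negligible. The simulation also makes drop-out depend on the previous observed score, the condition under which likelihood methods are valid, so it favours the mixed model by construction. The article does not say that descriptive statistics or post-hoc comparisons are restricted to completers, and an analysis plan not shown could add imputation. All of this stands and limits the size of the point. It does not remove it: the article names a method, and that method in its ordinary form deletes partial follow-up that the design expects.

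A reader might also draw three stronger conclusions, which the document does not support.
- That the plan foresees a loss of 17% or more. It states no two-year figure; 16.7% is only what 240 and 200 imply.
- That it contradicts itself by calling missing responses unlikely while sizing for drop-out. The sentence concerns answers within a questionnaire at each measurement time; drop-out is dealt with separately in the same section.
- That 240 is too few. The shortfall, 194 against 200 or 200/0.81 = 247 against 240, needs an assumed 10% in each year and is about 3%. The 200 was set by precedent for the networks, and 194 lies within the cited range of 172 to 342. The Discussion already concedes that the sample may prove too small.

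**Conclusion.** The point holds for the non-network variables only. As written, the MANOVA would exclude about 40 of 240 participants per cohort at the 16.7% loss that the enrolment figure allows, and about 46 if 10% a year is assumed, before any intermittently missed wave. Under these assumptions the cost is roughly 4% to 8% on the standard errors of the T1–T2 and T1–T3 changes, and wave means that describe completers. Bias in change over time is probably small, but that rests on the assumed correlation and drop-out mechanism. The direction matters because imprecision favours the fourth hypothesis. The conclusion assumes the classical form of the method, with no imputation specified elsewhere.

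The T4 size is not an error. At most, the authors could note that 200 remain at T4 only if two-year loss does not exceed 16.7%. This is a change worth making because it is cheap, not because the study fails without it.

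**What to change.** In Statistical analyses, replace the repeated measures MANOVA with a linear mixed model for repeated measures for each outcome: wave as a factor, cohort, wave by cohort, unstructured covariance across waves, all available waves included. State that it is valid if data are missing at random. Specify a multiplicity adjustment across outcomes and post-hoc contrasts, since several univariate models replace one multivariate test.

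In Design and procedures, add that forced answers prevent missing items but not missed waves. Optionally add the T4 note above, with about 194 per cohort as the figure if 10% a year is assumed.

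The cost is a few sentences of text and standard software, with no extra participants or data. The small downside is giving up the single multivariate test.
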